## Background

There is increasing interest in the use of police drug diversion (PDD) schemes. Following the review by Stevens et al. (2022), we define such schemes as alternatives to criminalisation for minor drug-related offences, including—but not limited to—simple possession for personal use. They are alternatives that provide people suspected of such offences with an educative or therapeutic intervention, rather than being processed through prosecution and conviction. Such diversion has a long history in English policing, going back at least to the 1930s,^1^ but its use for drug offences was not openly acknowledged until more recently. Several police forces in the UK and elsewhere are now operating such schemes (Shaw et al., 2022; Stevens et al., 2022). Their use is likely to expand as the government drives policy on ‘out-of-court disposals’ (OOCDs), as signalled in the White Paper on a *Smarter Approach to Sentencing* (MoJ, 2020) and by the subsequent Police, Crime, Sentencing and Courts Act 2022. OOCDs include a range of disposals available for use by the police in England and Wales which enable police officers to resolve cases without suspects being charged or prosecuted, of which PDD is one form (Shaw et al., 2022).

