## The evaluated PDD schemes

In collaboration with local stakeholders and based on Hoffmann et al.’s (2014) template for intervention description and replication (TIDieR) checklist, we have developed manuals which describe the operation of each of the PDD schemes in the three focus areas: Durham (Hendrie et al. (2023a), Thames Valley (Hendrie et al. (2023b) and the West Midlands (Hendrie et al. (2023c). Their common features are that they involve police contact with people who use drugs who are suspected of committing an offence (e.g. drug possession). We refer to this target group as ‘drug-involved suspects’. In each area, PDD involves diversion to group or individual sessions of drug education and advice instead of proceeding with prosecution for the suspected offence. People who are diverted may also be referred to other services (e.g. local drug treatment agencies) if needed. There are some differences between the three focus areas. In the West Midlands and Thames Valley, the interventions to which people are diverted are provided by third sector organisations and people generally receive online or face-to-face drug education sessions. Eligibility in these areas is confined to people suspected of simple drug possession (with no intent to supply). In Durham, the eligibility criteria include a wider range of offences. Here, the diversion takes the form of one-to-one meetings with staff employed by the police (known as ‘navigators’). These similarities and differences will be studied in our evaluation to examine the various mechanisms and outcomes which they trigger.

The overall study design is a mixed methods realist evaluation which combines a: qualitative assessment of the implementation, contexts, mechanisms, moderators and outcomes of the evaluated PDD schemes; with a quantitative, quasi-experimental analysis of administrative data on the effects of being exposed to the presence of PDD schemes on reoffending and health outcomes. These will be supplemented with analysis of the cost-consequences of the evaluated PDD schemes, an analysis of the equity of their implementation and effects, and a realist synthesis of the various findings from these different methods.

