### Work package 3: quantitative outcome assessment

A quantitative outcome assessment will test hypotheses that the presence of PDD schemes in police force areas reduce adverse health and offending outcomes for drug-involved suspects. The analysis will involve comparing outcomes for cohorts of drug-involved suspects eligible for diversion in our three focus areas (i.e. police forces with PDD schemes), with those for cohorts of similar individuals in three comparison areas (i.e. forces without PDD schemes) that are in groups of police forces that are most comparable to the intervention forces (HMICFRS, 2023).

Participants in our quantitative analysis will be individuals who had contact with the police in relation to illicit drugs, who may have been eligible for diversion (regardless of whether diversion was available, offered or taken up by that individual). Each PDD and comparison police force will identify individuals who had contact with the police for a qualifying offence between 1 October and 2021 and 30 September 2022 and were aged at least 18 years. Qualifying offences will be (a) simple possession of any controlled drug (personal use), and (b) any of: shoplifting, assault, criminal damage, criminal damage without intent to commit, possession of drugs, drunk and disorderly, drunk and incapable, any theft (other than burglary); in combination with a suspected or proven offence in contravention of the Misuse of Drugs Act 1971 or the Psychoactive Substances Act 2016, in the preceding 3 years, OR a flag in police records for involvement with illicit drugs.

We will use two primary outcomes for health and reoffending:

Health—the count of hospital episodes (including unplanned/emergency inpatient admissions and emergency department visits) during the follow-up period that are related to drugs, alcohol, or accidents.Reoffending—a count of how many offences participants commit in the follow-up period, as recorded in the PNC and adjusted for the time that each participant was in the follow-up period.

We will also use the following secondary outcomes:

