Health—the measures will be (a) any entry into structured treatment for drug or alcohol use in a community setting during the follow-up period; and (b) retention in treatment for at least 28 days for those who start drug or alcohol treatment.Reoffending—(a) a dichotomous measure of any offending, with analysis offset by the duration of follow-up, and (b) a measure of the total social cost of these crimes, calculated using the costs attributed to each type of crime according to Home Office estimates of the social costs of each type of crime (Heeks et al., 2018).

The data for the quantitative impact assessment will be compiled using individual-level data linkage between databases of administrative records. Participating police forces will share lists of eligible individuals with the Department of Health and Social Care (DHSC), which is a partner in the project. The DHSC will link the data to four national health and criminal justice databases, and then pseudonymise the data before analysis within a secure data system. The four national databases will be:

The Police National Computer, which will be used to derive a measure of historical offending at study entry, and the primary and secondary reoffending outcomes;The National Drug Treatment Monitoring System, which will be used to measure secondary health outcomes (i.e. entry to and retention in drug and alcohol treatment services);Hospital Episode Statistics, which will be used to measure our primary health outcome (i.e. hospital episodes) (Herbert et al., 2017).The Office for National Statistics mortality database, which we will use to identify participants who die during the follow-up period and are to be excluded from our analysis. Deaths will only be used to censor follow-up and not as an outcome because their relative rarity would result in a lack of statistical power for detecting significant effects.

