The social and economic costs associated with reoffending (e.g. arrests, convictions and imprisonments) as quantified in work package 3 will be included in the CCA. We will apply unit costs for each criminal justice event recorded in the data linkage. Treasury approved methods will underpin the CCA and unit costs will be extracted from the latest version of the Greater Manchester Combined Authority Unit Cost Database and the Home Office estimates of the costs of crime (GMCA Research Team, 2021; Heeks et al., 2018). This will cover the costs of crime, health and social services. Costs of crime will be presented in terms of fiscal costs and cost to society. The domains for the CCA for the 12 months following police contact are the cost of hospital admissions relating to acute mental health, alcohol and other drugs, and the criminal justice system costs of criminal conviction.

Costs will be presented in a disaggregated format which will provide clear information to the different stakeholders with respect to their financial impacts. The CCA will estimate the longer-term discounted costs over the next five years based on criminal justice contacts and health care episodes. We will construct a hybrid decision tree and Markov model based upon drug use status following PDD. The model uses the rates of post-PDD drug use, all cause death rates, and reconviction rates as transition probabilities. A mean patient cost for health care and criminal justice in each of the Markov states is applied and the simulation will be run for a period of five years. Costs and outcomes occurring beyond one year are discounted using a discount rate of 3.5% as recommended by the National Institute for Health and Clinical Excellence (NICE, 2020). We will use the NHS National Costs Collection and GMCA database combined with data from work package 3 and parameters from the published literature to estimate the return on investment. The costs of the PDD programme will also be scaled up to national level in order to estimate the overall cost of providing the intervention it if were to be nationally implemented.

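### Reoffending is counted from PNC records alone while the exposure alters how offences are disposed of, so the count needs a disposal-neutral rule and a check on non-divertible offences

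*Protocol article*

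**What the plan says.** **Outcome.** The Protocol article, under Work package 3: quantitative outcome assessment, defines the primary reoffending outcome as "a count of how many offences participants commit in the follow-up period, as recorded in the PNC", adjusted for time in follow-up. The secondary reoffending outcomes are any offending and the social cost of the offences. The same section lists the PNC as the database "which will be used to derive a measure of historical offending at study entry, and the primary and secondary reoffending outcomes". No other source of reoffending data is named.

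**Exposure.** The Background says people in these schemes receive an educative or therapeutic intervention "rather than being processed through prosecution and conviction". It places the schemes among out-of-court disposals that "enable police officers to resolve cases without suspects being charged or prosecuted, of which PDD is one form". The section The evaluated PDD schemes says that each area uses "diversion to group or individual sessions of drug education and advice instead of proceeding with prosecution for the suspected offence". Eligibility is confined to simple possession in Thames Valley and the West Midlands; "In Durham, the eligibility criteria include a wider range of offences".

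**Contrast.** Three forces with a scheme are compared with three without. The primary analysis takes all eligible suspects, diverted or not, and adjusts for individual covariates and for each force's baseline probability of the outcome.

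**Economic model.** Work package 4 states: "The model uses the rates of post-PDD drug use, all cause death rates, and reconviction rates as transition probabilities".

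**The concern.** The outcome is read from a criminal justice record, and the exposure acts on the process that produces such records. A divertible offence committed during follow-up may take one administrative route in a scheme force and another in a comparison force. If the routes differ in how completely they reach the count, ascertainment depends on exposure. The estimated rate ratio then mixes any change in behaviour with a change in recording.

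This does not require anyone to be diverted twice. The primary analysis includes people who were not diverted at entry, and their first diversion can fall within follow-up.

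Both secondary reoffending outcomes use the same source and so give no independent check. The stakes are practical: the Dissemination section makes national guidelines conditional on a positive impact and says that spending cases may draw on one.

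**Working it through.** The article gives no event rate, sample size or effect size for work package 3, so there is no figure of the plan's own to reproduce. Every numerical input below is an assumption.

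**Inputs**
- s: share of follow-up offences of a divertible type.
- d1, d0: share of those resolved by diversion or another out-of-court route, in scheme and comparison forces.
- u1, u0: share of offences so resolved that do not enter the count.
- True behavioural effect: none (rate ratio 1).

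**General form**

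Apparent rate ratio = (1 − s·d1·u1) / (1 − s·d0·u0)

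**Case A: all diverted offences uncounted, nothing lost in comparison forces** (u1 = 1, d0·u0 = 0). The form reduces to 1 − s·d:

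| s | d = 0.25 | d = 0.50 | d = 0.75 |
|---|---|---|---|
| 0.1 | 0.975 | 0.950 | 0.925 |
| 0.2 | 0.950 | 0.900 | 0.850 |
| 0.3 | 0.925 | 0.850 | 0.775 |
| 0.4 | 0.900 | 0.800 | 0.700 |

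**Case B: half of the diverted offences uncounted** (u1 = 0.5). With s = 0.3 and d = 0.5: 1 − 0.3 × 0.5 × 0.5 = 0.925.

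**Case C: diverted offences fully counted** (u1 = u0 = 0). The ratio is 1.00 for every s and d.

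**Case D: comparison forces also lose out-of-court cases** (u1 = u0 = 1, s = 0.3, d1 = 0.5):
- d0 = 0.25: 0.85 / 0.925 = 0.92
- d0 = 0.50: 0.85 / 0.85 = 1.00
- d0 = 0.75: 0.85 / 0.775 = 1.10

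The sign therefore depends on practice in the comparison forces.

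**Net-widening.** Work package 5 raises this possibility. If a scheme raised recorded offences by a factor 1 + w, the 0.85 of Case A would be cancelled at 1 + w = 1/0.85 = 1.18.

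**What a larger sample does.** Assume a mean count of 1, dispersion k = 2, n per group, and no clustering. For log rate ratio, SE² = (1/μ1 + k)/n + (1/μ2 + k)/n. With a spurious ratio of 0.90 and n = 1,000:
- SE² = (3 + 3.111)/1,000 = 0.00611, so SE = 0.0782
- z = 0.1054/0.0782 = 1.35
- probability of two-sided significance at 0.05: 0.27

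At n = 3,000 it is 0.65 and at n = 10,000 it is 0.99. More data makes such an artefact more likely to reach significance, if it exists.

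**The restricted count.** For offence types that no scheme can divert, s = 0 and the ratio is 1.00 whatever d and u are. The price is fewer events. If s = 0.4, a mean of 1 falls to 0.6. With k held at 2, the SE grows by √[(1/0.6 + 2)/(1 + 2)] = √(3.667/3) = 1.11, about 11%.

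**The case against.** **The premise is not documented.** Nothing in the article says that the PNC omits diverted offences or that a person can be diverted again. Work package 4 gives arrests among its examples of reoffending events quantified in work package 3, and arrest precedes disposal. This stands: the bias is a possibility, not an established fact.

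**Condensation.** Which PNC entries count may be settled in a fuller protocol or analysis plan. That is fair, and the silence alone is not the point. The point is the pairing that the article does fix: one source for all reoffending outcomes, and an exposure that changes disposal. If a fuller document already counts offences whatever the disposal in all six forces, the concern about the count is met.

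**Comparison forces also use out-of-court disposals, and net-widening may raise counts.** Both stand. Case D and the net-widening calculation show that the bias could vanish or reverse.

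**Safeguards exist.** They help only in part:
- A baseline probability from before the scheme cannot capture recording that the scheme changes. One from during the scheme may absorb real effect. The article does not give its window.
- The by-force test can set Durham apart but cannot separate recording from behaviour.
- The yearly aggregate counts of diversions, out-of-court disposals and sanctions in work package 2 cover only the three focus areas.
- The hospital outcome is unaffected, but it does not test reoffending.

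**Economic model.** A reader might infer that reconviction is lower by construction. The documents do not support that: the model also draws on published parameters, and the source of the reconviction rates is not given. Fewer convictions are also a genuine cost consequence. What stands is that a lower reconviction rate, taken alone, does not show less crime.

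**Conclusion.** The concern holds as a conditional one. Ascertainment of divertible offences can depend on exposure, all three reoffending outcomes share the source, and no analysis described in the article separates recording from behaviour. Size and direction are unknown. The range 0.975 to 0.70 rests on assumed s of 10% to 40% and d of 25% to 75%, complete loss of diverted offences, and no loss in comparison forces. Under identical counting in all six forces the bias is nil.

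A reader might infer that a positive result would be purely a recording effect, or that the reoffending hypothesis cannot be tested. Neither follows from a possible bias of unknown size and sign. Nor do the documents require a new primary outcome built on force-specific exclusion lists. The article describes three comparison areas, not matched pairs, and does not list Durham's eligible offences. Different outcome definitions in different forces would also muddle a pooled rate ratio. A common counting rule with a restricted check is enough to determine what a positive result can support.

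**What to change.** 1. Keep the all-offence PNC count as primary, but define it by offence, whatever the disposal, with the same rule in all six forces. Where the PNC does not hold a diverted or other out-of-court offence, take it from force records. Use the same rule for any offending, social cost and the offending-history covariate.
2. Pre-specify a sensitivity analysis of the count and of any offending, restricted to offence types not eligible for diversion in any focus area. Draw one exclusion list from the three scheme manuals and apply it to all six forces.
3. State in advance that reduced offending will not be claimed from the all-offence count unless the restricted analysis is consistent with it.
4. In work package 4, report a lower reconviction rate as a criminal justice cost consequence, and do not read it alone as less crime.

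**Cost.** An offence-code filter, some wording, and possibly a small additional request to forces that already supply individual lists. The restricted analysis has fewer events and lower precision. The loss could be considerable if Durham's list is broad, and the analysis cannot detect a real fall confined to divertible offences. It is therefore a check on the primary result, not a replacement for it. The rules should be fixed before outcome data are extracted.

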There have been randomised trials of some such schemes—including Turning Point in the West Midlands and Checkpoint in Durham—for their effects in reducing offending, with generally positive results (Neyroud, 2018; Weir et al., 2021, 2022). Less is known about the contexts and mechanisms of such programmes in the UK, and about their effects on outcomes other than offending—particularly health outcomes. People who use drugs are highly vulnerable to a range of health harms, not only from overdose, but also from chronic health conditions (Lewer et al., 2021). PDD schemes offer the opportunity to divert people towards drug treatment services that are effective in treating substance use disorders and preventing death (Ma et al., 2019; Stevens et al., 2022). To develop useful knowledge on the contexts, mechanisms, moderators and outcomes of PDD, we decided to carry out a realist evaluation of PDD schemes in England (Pawson & Tilley, 1998). Realist evaluation enables us to move beyond analysing what works in PDD to consider what works, for whom, in what circumstances and why. The work has been co-designed with our policing partners and with User Voice, a charity led by people with lived experience of adverse contact with criminal justice agencies. It is funded by the Cabinet Office Evaluation Accelerator Fund, which aims to build the evidence base on priority policy areas with a view to informing future government spending reviews.

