This theory of change was based on the programme theory provided by Stevens et al.’s (2022) realist review of alternatives to criminalisation for drug possession, with additional input from research published since the search was carried out for this review (in 2018). This additional research was found using similar search terms and databases to those used in the original review. The theory was further developed through discussion with stakeholders at the local and national workshops. The resulting theory of change is available online as a separate document (Stevens et al., 2023). In summary, it suggests that PDD may have positive effects on offending and health outcomes via two causal pathways. One is avoidance of the negative effects of criminalisation. The other is enhancing the support and treatment available to people who are at risk of drug-related offending and health harms. The theory of change also identifies a range of relevant contexts and moderators of the outcomes of PDD, as displayed in Fig. 1.

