We plan to use multivariable regression to estimate the effect of PDD on primary and secondary outcomes. Our analysis will control for potential confounders including age, sex/gender, ethnicity, health, previous experience of drug or alcohol treatment, offending history, reason for police contact, date of cohort entry, and the force-level baseline probability of each outcome. Our primary outcomes are count variables, and we will therefore use a mixed negative binomial model offset by the logged duration between the study entry date and the end of follow-up. We plan to use a negative binomial model rather than a Poisson model because we anticipate that both outcomes will be overdispersed, with some participants having high counts.

In our primary analysis, we will compare outcomes for all drug-involved suspects eligible for diversion in our focus areas (regardless of whether they were offered or took up diversion) with those for similar suspects in control areas. This is akin to an ‘intention to treat’ design in an experimental study (Hernán & Robins, 2016).

In our secondary analyses, we will:

Compare outcomes for participants who are diverted with those who are not. This is comparable to a ‘per protocol’ analysis in experimental trials (Hernán & Robins, 2016);Report access to diversion by age, sex, ethnicity, and socioeconomic status (as a complement to work package 5 on equity of effects).Test whether the effectiveness of diversion for each outcome varies by police force (while acknowledging that this analysis will have lower statistical power).

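### 28-day retention is defined only among people who start treatment, a group PDD is intended to change, so its contrast is not a clean effect of PDD and can point the wrong way

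*Protocol article*

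**What the plan says.** The section on work package 3 lists two secondary health outcomes. Outcome (a) is "any entry into structured treatment for drug or alcohol use in a community setting during the follow-up period". Outcome (b) is "retention in treatment for at least 28 days for those who start drug or alcohol treatment". So (a) is not restricted to starters, while (b) has starters as its denominator.

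The same section states the use of these outcomes: "We plan to use multivariable regression to estimate the effect of PDD on primary and secondary outcomes". For the primary analysis it says "we will compare outcomes for all drug-involved suspects eligible for diversion in our focus areas" with similar suspects in control areas, whether or not diversion was offered or taken up, and likens this to intention to treat.

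Three other sections link PDD to treatment entry:

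- Background: "PDD schemes offer the opportunity to divert people towards drug treatment services".
- The evaluated PDD schemes: "People who are diverted may also be referred to other services (e.g. local drug treatment agencies) if needed".
- Work package 1, on the second of the two causal pathways: "The other is enhancing the support and treatment available to people who are at risk of drug-related offending and health harms".

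The article does not define retention over the whole cohort, does not say how selection into starting would be handled, and does not label (b) as descriptive.

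**The concern.** Whether a suspect starts treatment is observed after exposure to a PDD area, and the schemes are meant to influence it. Even if the two cohorts were perfectly balanced at entry, the starters within them need not be. Starters in PDD areas may include people who would not have started otherwise, and comparison areas have no counterpart to them. The starters-only contrast then mixes two things: any effect on how long people stay, and a change in who starts.

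The planned adjustment uses baseline characteristics such as health, previous treatment and offending history. These may capture part of the difference between usual and extra starters. Motivation and current severity of dependence are not named, so adjustment cannot be relied on to remove the selection.

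At stake is the reading of one of the two secondary health outcomes. A scheme that brings more people into treatment and keeps more of them there could be reported as worsening retention. The planned comparison of effectiveness by police force would carry the same problem: a force that draws in more marginal starters could look worse. The cost-consequence analysis builds on the work package 3 outcomes, and the Dissemination section foresees use of the results in spending cases and policing guidelines.

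**Working it through.** The article states no entry rate, retention rate, sample size or power for this outcome, so there is no figure to reproduce. Every rate below is an assumption, and a range is shown.

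**Inputs**

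- e0: share of eligible suspects who start treatment without PDD; assumed 10%.
- r0: 28-day retention in these usual starters without PDD; assumed 70%.
- d: change in usual starters' retention under PDD; 0 at first, then +5 points.
- x: extra share who start because of PDD; 2, 5 or 10 points (entry up 20%, 50% or 100% in relative terms).
- r1: retention in the extra starters; 40% to 80%.

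**Formulas**

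- Among starters: [e0(r0 + d) + x·r1] / (e0 + x) with PDD, against r0 without.
- Whole cohort, entered and retained: e0(r0 + d) + x·r1 with PDD, against e0·r0 without.
- The starters-only difference is negative when r1 < r0 − d·e0/x. The whole-cohort difference is positive when x·r1 + e0·d > 0.

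**Worked case**, d = 0, entry 10% to 15%, r1 = 50%

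- Among starters: (0.10 × 0.70 + 0.05 × 0.50) / 0.15 = 0.095 / 0.15 = 63.3%, against 70.0%. The difference is −6.7 points (odds ratio 0.74).
- Whole cohort: 9.5% against 7.0%. The difference is +2.5 points.

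**Range**, d = 0. Each cell gives the starters-only difference, then the whole-cohort difference, in percentage points.

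| r1 | Entry 10% to 12% | Entry 10% to 15% | Entry 10% to 20% |
|---|---|---|---|
| 40% | −5.0 / +0.8 | −10.0 / +2.0 | −15.0 / +4.0 |
| 50% | −3.3 / +1.0 | −6.7 / +2.5 | −10.0 / +5.0 |
| 60% | −1.7 / +1.2 | −3.3 / +3.0 | −5.0 / +6.0 |
| 70% | 0.0 / +1.4 | 0.0 / +3.5 | 0.0 / +7.0 |
| 80% | +1.7 / +1.6 | +3.3 / +4.0 | +5.0 / +8.0 |

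For a given relative rise in entry, the starters-only figures do not depend on e0. The whole-cohort figures scale with it.

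**If PDD also helps usual starters**, d = +5 points. With entry 10% to 15% and r1 = 50%:

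- Among starters: (0.10 × 0.75 + 0.05 × 0.50) / 0.15 = 0.100 / 0.15 = 66.7%. The difference is −3.3 points (odds ratio 0.86).
- Whole cohort: 10.0% against 7.0%. The difference is +3.0 points.

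The value of r1 below which the sign reverses is 70 − 5 × 10/2 = 45% for entry up 20%, 70 − 5 × 10/5 = 60% for entry up 50%, and 70 − 5 × 10/10 = 65% for entry up 100%.

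**The case against.** The strongest case against has four parts.

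- **The direction is not known.** The documents give no data on who the extra starters would be. A reader might infer that they will be less severe cases who drop out sooner, but nothing in the article supports that as fact. The r1 = 70% and 80% rows show that the reversal then disappears. This stands: the claim can only be that the contrast may mislead.
- **A large rise in entry may be unlikely.** The comparison covers all eligible suspects, including those never diverted. Diversion in two of the three areas is generally drug education, and referral to treatment is made only where needed. The theory-of-change pathway also covers support as well as treatment, and speaks of availability rather than entry. This stands for size: at the mild end of the reversing range the distortion is −1.7 points. It does not remove the link to entry, which the Background and the description of the schemes also state.
- **Partial safeguards exist.** Outcome (a) sits beside (b), so a reader can see a rise in entry and combine the two. The adjustment list is open and includes health and previous treatment. Both help, but neither makes the starters-only contrast an unbiased effect of PDD.
- **Retention among starters is a fair question about engagement.** It is, and it can still be reported. The objection is to estimating it as an effect of PDD.

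A reader might also infer that people who start treatment in the last 28 days of follow-up cannot meet the definition. The text does not support this. It attaches the follow-up period to entry, outcome (a), and does not say that observation of retention stops there.

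**Conclusion.** The concern holds in a limited form. Outcome (b), as the article defines it, conditions on an event that PDD is intended to change, and the plan to estimate the effect of PDD on it has no stated safeguard beyond baseline adjustment. It is not a clean effect of PDD.

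Under the assumed rates with d = 0 and extra starters retained at 40% to 60%, the starters-only difference runs from −1.7 to −15.0 points while the whole-cohort difference runs from +0.8 to +6.0 points. The ends of these two ranges do not all come from the same scenarios; the table gives the pairs. Reversal is possible, not inevitable: it needs extra starters who are retained sufficiently less often than usual starters. The documents do not say whether they would be.

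The point touches one secondary outcome. The primary outcomes, treatment entry and the reoffending outcomes are not affected. It should be changed because the remedy is cheap and follows the plan's own comparison of all eligible suspects.

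**What to change.** Redefine the inferential outcome (b) as having entered structured treatment and been retained for at least 28 days, among all eligible suspects, with non-starters coded as no. Report retention among starters beside it as descriptive, with a caveat that it is not a causal effect of PDD because PDD may change who starts.

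The cost is wording. The planned linkage to the National Drug Treatment Monitoring System already supplies entry and retention, so no further data are needed. The drawback is small: nobody can be retained without entering, so the new outcome overlaps with (a), and the two should be read together. The change removes selection on starting treatment only. Confounding between PDD and comparison areas still rests on the planned adjustment.
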